7.53 Virus Detection

Percentages will be described using exact confidence intervals. This will be done separately for men and women with respect to detecting virus in genital secretions.

Subjects analyzed will be those who have a week 48 specimen available and have persistently suppressed blood plasma viral loads (< 200 copies/mL) from week 16 through week 48.

7.54 Virologic Events

The assessment of differences in virologic events between blood and nonblood compartments will be based on the nonparametric sign test. Only those subjects in whom it can be determined which event (blood versus nonblood) occurred earlier will contribute to the analysis; the interval-censored nature of the data will be considered in making this determination.

# HUMAN SUBJECTS

## Institutional Review Board (IRB) Review and Informed Consent

This protocol and the informed consent document (Appendix VI) and any subsequent modifications will be reviewed and approved by the IRB or ethics committee responsible for oversight of the study. Written and signedinformed consent will be obtained from the subject (or parent, legal guardian, or person with power of attorney for subjects who cannot consent for themselves, such as those below the legal age). The subject’s assent must also be obtained if he or she is able to understand the nature, significance, and risks associated with the study. The consent form will describe the purpose of the study, the procedures to be followed, and the risks and benefits of participation. A copy of the consent form will be given to the subject (or parent or legal guardian).

## Subject Confidentiality

All laboratory specimens, evaluation forms, reports, and other records will be identified by a coded number only to maintain subject confidentiality. All records will be kept in a locked file cabinet. All computer entry and networking programs will be done with coded numbers only. Clinical information will not be released without written permission of the subject, except as necessary for monitoring by the NIAID.

## Study Discontinuation

The study may be discontinued at any time by the NIAID.

# PUBLICATION OF RESEARCH FINDINGS

Publication of the results of this trial will be governed by ACTG policies.

# BIOHAZARD CONTAINMENT

As the transmission of HIV and other blood-borne pathogens can occur through contact with contaminated needles, blood, and blood products, appropriate blood and secretion precautions will be employed by all personnel in the drawing of blood and shipping and handling of all specimens for this study, as currently recommended by the Centers for Disease Control and Prevention.

All infectious specimens will be sent using the ISS-1 SAF-T-PAK mandated by the International Air Transport Association Dangerous Goods Regulations-Packing Instruction 602. Please refer to individual carrier guidelines, e.g., FedEx, Airborne, for specific instructions.

| Pregnancy test (urine or serum ß-HCG)4 | X | Anytime pregnancy is suspected | | | | | | | | | | | | | |  |
| Hematology 5 |  | X | X | X | X | X | X | X | X | X | X | X | X | X | X | X |
| CD4/CD8 cell count6 |  | X | X | X | X | X | X | X | X | X | X | X | X | X | X | X |
| HIV-1 RNA (real time) 6 |  | X | X | X | X | X | X | X | X | X | X | X | X | X | X | X |
| Plasma/PBMC collection & storage7 |  |  | X |  | X |  |  |  | X |  |  |  |  |  | X | X |
| Saliva collection8 |  |  | X |  | X |  |  |  | X |  |  |  |  |  | X | X |
| Genital secretions collection9 |  |  | X |  | X |  |  |  | X |  |  |  |  |  | X | X |
| Lymphoid tissue collection9 |  |  | X |  | X |  |  |  | X |  |  |  |  |  | X | X |

1 Screening: complete clinical assessment to include a history of all HIV-related diagnoses and AIDS-defining events, and a signs and symptoms assessment with symptom-directed physical exam. If any signs or symptoms of a genitourinary tract infection are noted, the subject should be evaluated and treated for at least 14 days and the infection considered resolved prior to entry.

On Study/Virologic Failure/Premature Discontinuation Visits: clinical assessment to include updated signs/symptoms and new HIV-related diagnoses.

2 Targeted physical exam to include signs/symptoms and new HIV-related diagnoses. If any signs or symptoms of a genitourinary tract infection are noted, the subject should be evaluated and entry delayed until the subject has been treated for at least 14 days and the infection is considered resolved.

3 Medication history to include all anti-HIV medications, immune-based therapies, and HIV vaccines ever taken prior to study entry. Medication updates to include changes in anti-HIV medications, immune-based therapies, and HIV vaccines.

4 Pregnancy test must be performed within 14 days of entry and any time pregnancy is suspected.

5 CBC with differential required only if CD4/CD8 cell counts will be measured at this visit.

6 If CD4/CD8 cell counts or HIV-1 RNA levels are measured as part of a coenrolled study at the same time as an A5077 protocol visit, or total blood volumes exceed safe limits, they do not need to be repeated for A5077. If available, the results should be obtained and entered onto the appropriate A5077 CRF. If HIV-1 RNA levels are measured as part of A5077, see Appendix II for collection, processing, storage, and shipment information.

7 Required unless total blood volumes exceed safe limits. See Appendix II for collection, processing, and storage information.

8 Saliva collection required of all subjects (see Appendix III).

9 Subjects have the option to contribute either genital secretions or lymphoid tissues, or both (see Appendix IV and V).

BLOOD COLLECTION, PROCESSING, STORAGE, AND SHIPMENTPROCEDURES

1.0. OVERVIEW OF VIROLOGIC EVALUATIONS

Unless total blood volumes exceed safe limits (the American Red Cross has a limit of 450 mL of blood over 56 days for healthy volunteers), all subjects will have blood samples obtained for real-time HIV-1 RNA levels at preentry, entry, week 8 and every 8 weeks thereafter until week 96, within 30 days of confirmed virologic failure, and at the premature study discontinuation visit. Plasma and PBMCs will be collected and stored at entry, weeks 16, 48, and 96, within 30 days of confirmed virologic failure, and at the premature study discontinuationvisit.

NOTE: If total blood volumes exceed safe limits and do not permit an A5077 blood draw, the A5077 protocol team will prioritize requests for access to specimens in the following order of priority: 1) one plasma aliquot (1.5 mL); 2) one aliquot of frozen PBMCs (> 2 x 106 cells).

Virologic studies planned include the following:

- Quantitation of HIV-1 RNA levels in plasma using the UltraSensitive Roche assay.
- Genotypic resistance studies (analysis of HIV-1 reverse transcriptase and protease sequences) in plasma.
  NOTE: DNA extracted from PBMC will be used for genotypic resistance studies when plasma HIV-1 RNA levels are low (< 1000 HIV RNA copies/mL).
- Detection and quantitation of HIV-1 proviral DNA (total and 2-LTR circles) in PBMC fractions using an in-house assay.

2.0 SPECIMEN COLLECTION, PROCESSING, AND STORAGE

NOTE: SPECIMENS MUST BE DELIVERED TO THE LABORATORY AND PROCESSED WITHIN 48HOURS OF COLLECTION

A. Specimen Collection

ONE 10.0 mL purple-top EDTA tube (Becton Dickinson re-order number #6457) will be drawn from all subjects at preentry,entry, week 8 and every 8 weeks thereafter until week 96, within 30 days of confirmed virologic failure, and at the premature study discontinuationvisit.

B. Specimen Processing

1. Clarified plasma

To minimize RNA degradation, all plasma samples must be processed and stored at -70°C within 48 hours of collection. Although the required processing time has been increased from 4-6 hours to 48 hours, sites are encouraged to continue to process HIV-1 RNA samples as soon as possible. Specifically, the EDTA tube should be centrifuged at low speed (400 x *g*) for 10 minutes at room temperature as soon as possible after collection.

Plasma should be carefully removed from each tube, placed in a sterile polypropylene conical centrifuge tube and centrifuged again (at 800 x *g*) for 10 minutes to completely remove platelets and cell debris. Store as many 1.2 mL aliquots of plasma as possible at –70°C.

2. PBMCs

After plasma has been removed as indicated above, PBMCs will be obtained and stored according to procedures outlined in the AACTG Virology Manual for HIV Laboratories (January 1997 version).

Store TWO TO FOUR aliquots of 2 x 106 cells as NON-VIABLE DRY cell pellets at - 70°C.

C. Real Time Plasma HIV-1 RNA

NOTE: Participating sites should try to avoid virologic sampling for confirmatory testing during an intercurrent illness, within 14 days after a subject receives an immunization or within 14 days of a dose interruption, as this may result in a transient elevation of plasma HIV-1 RNA levels.

Within ten (10) business days following the receipt of a plasma sample(s) by the ACTG-specified laboratory for the performance of real time plasma HIV-1 RNA assays, the designated laboratory will FAX the results to the clinic. Upon receipt, the clinic is to key the results into the central ACTG database.

If the result provides the first suggestion of a virologic failure, the subject should be recalled to the clinic to have a confirmatory virologic (plasma) specimen obtained. Every attempt should be made to have the confirmatory sample drawn as soon as possible, but no later than 30 days after the date of the first sample.

Results confirming study endpoints should be referred for verification as soon as possible to the protocol team via the [name] e-mail group, to the attention of the protocol chair or vice chair(s). When sending a request for verification of a study endpoint, the site should include the following information: PID, HIV-1 RNA values, and date of draws for 1) the first time point of failure and 2) the confirmatory sample.

TWO 1.2 mL aliquots of plasma for HIV-1 RNA determinations must be shipped (frozen on dry ice) via overnight, priority express to the contracting laboratory at Johns Hopkins University (JHU). Shipping instructions and how to obtain shipping materials are provided below.

All aliquot vials should be labeled with the PID, study number, unique identifier, VID, date drawn, and derivative (p12)/anticoagulant (EDTA).

All plasma HIV-1 RNA assays will be done at [name] laboratory atJHU using the Roche UltraSensitive assay. [name] laboratory will send sites the proper shipping containers and supplies. Sites need to contact the JHU laboratory (phone number below) to ask that shipping materials be sent. When calling, please provide the contact person and shipping address where the materials are to be sent.

For shipments of more than 15 vials, the 1.2 mL plasma samples should be placed in the Nalgene 5x5 or 9x9 cryovial box in the order of the shipping manifest (if the LDMS program is available). If fewer than 15 vials are to be sent, they can be placed in plastic baggies inside the orange-top shipping container. Each vial should be individually bagged or wrapped prior to placing in baggies. The 5x5 cryovial box should be securely covered and placed in the orange-top container or in an IS2 certified (STP 370) shipping container filled with carbon dioxide (dry ice).

The orange-top container should have absorbent material included. The container is then placed in the cardboard box, which is placed inside the polystyrene insulated box and the box filled with sufficient dry ice to last at least 48 hours. DO NOT PLACE DRY ICE INSIDE THE ORANGE-TOP CANISTER! Likewise, the Nalgene 9x9 or 5x5 cryovial box should be wrapped in absorbent material and placed inside a shipping plastic bag, sealed, and placed in an IS2 certified (STP 370) shipping container filled with dry ice.

The outer box is sealed with tape and marked with the appropriate stickers. Follow IATA/ICAO and ACTG shipping guidelines for the shipment of infectious (see section6.2) materials. The Virology Tracking Form should accompany the specimens to thelaboratory.

D.Paperwork

An LDMS shipping diskette, shipping manifest, and box map (if appropriate) must accompany the shipment as well as the tracking form. This material should not be placed in the dry ice, but in a plastic bag between the polystyrene container and outer box or outside the foam area of the IS2 certified shipping container. If the site does not have the LDMS, an ACTG Virology shipment notice, duplicate Virology Tracking Form, and a list of specimens being sent (box map) should be included with the shipment. ALWAYS include an inventory with every shipment. The inventory must include complete information--PID, study number, draw date, VID (if week 0, indicate if screen, preentry, or entry), clinic number, number of aliquots, volume, position in box, AND sending laboratory information. The inventory may be in the form of a spreadsheet, typed or legibly handwritten. (Mini-programs are available through FSTRF to create both spreadsheets and diskettes.)

The samples and appropriate paperwork should be sent to:

[name]

ATTN: [name]

Department of Pathology - Johns Hopkins University

[name]

[name]

[name]

[contact]

[contact]

E-mail: [contact]

Prior to shipment, please FAX the ACTG Virology Shipping Notice to [name] at [contact]. If the FAX does not seem to be transmitting, please call the laboratory at [contact] to advise that a shipment has been sent and provide the airway bill number. Any questions relating to specimen handling, shipping, or identification should be directed to [name] at [contact].

Please call the laboratory around holiday times to check available days for shipping.

Shipments may be made Monday through Wednesday only by overnight courier service (Federal Express) and billed to the recipient (Fed Ex acct. number 2182-1427-4). The laboratory is not open to receive shipments on weekends or holidays. The Federal Express forms will be provided.

E. Specimen Storage

All other plasma and PBMC aliquots are to be stored frozen and shipped to the repository per the AACTG guidelines (see F below).

F. Instructions for Shipping to the Repository

Unless otherwise stated, stored samples should be shipped to the repository. Please refer to the AACTG web site at: <http://aactg.s-3.com/specrepos.htm> for complete instructions on packaging, shipping, and repository notification.

SALIVA COLLECTION, PROCESSING, STORAGE, AND SHIPMENT PROCEDURES

1.0 MATERIAL NEEDED

- 50-mL sterile centrifuge tube with screw-on cap
- Plastic or paper cup containing wet ice
- 2.0-mL cryostorage tubes with screw-on caps
- Labels
- Sterile pipettes
- Aerosol-resistant pipette tips
- Slow-speed table-top centrifuge

2.0 SPECIMEN COLLECTION

All study subjects will have saliva samples collected at study entry, weeks 16, 48, and 96, within 30 days of confirmed virologic failure, and at the premature study discontinuation visit.

After obtaining informed consent, ask the subject to expectorate into a sterile 50-mL centrifuge tube, which is kept cool on wet ice. Note that the subject is not to have eaten or brushed his/her teeth within 30 minutes of sample collection. A total of 5 mL of whole unstimulated saliva should be collected (procedure may take 5-15 minutes depending on subject’s salivary flow rate). Label the tube with PID, SID, and date. The sample should be frozen at -20ºC within 2 hours of collection and stored on site at -80° C until shipped on dry ice to the repository (see section 4.0).

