3.0 SPECIMEN PROCESSING

1. Measure the sample volume and record (in mLs).

2. Vortex the specimen briefly and then transfer two 1-mL aliquots of whole saliva to sterile labeled cryostorage tubes using a sterile 5-mL pipette. This untreated saliva is referred to as “whole saliva.”

3. Salivary cells are recovered from the remaining saliva sample as follows. Recap the tube containing the sample and centrifuge at 400 x *g* at 4°C for 10 minutes to pellet the cells, cellular debris, and mucins.

4. Remove the supernatant with a 5-mL pipette and transfer 1-mL aliquots to sterile, labeled cryovials. Label as cell-free saliva.

5. Add 30 mL cold sterile phosphate-buffered saline (PBS) to the tube containing the saliva cell pellets, recap the tube, and resuspend the pellets by gently vortexing for 10-15 seconds.

6. Centrifuge the cell suspension at 400 x *g* at 4°C for 5 minutes.

7. Remove and discard the supernatant.

8. Repeat the washing procedure once more.

9. After the final wash, remove all of the supernatant. Resuspend the cell pellets in 1 mL of cold PBS, remove a small aliquot (~20 µL), and count the cells using the hemocytometer and record.

10. Transfer the cell suspension to sterile cryovials in 0.5-mL aliquots.

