5.0 ANALYSIS

Virologic studies planned include the following:

- Quantitation of HIV-1 RNA levels in saliva using the Organon Teknika NucliSens HIV-1 RNA QT assay.
- Detection and quantitation of HIV-1 proviral DNA (total and 2-LTR circles) in salivary cells using an in-house assay.
- Genotypic resistance studies (analysis of HIV-1 reverse transcriptase and protease sequences) in saliva.
  NOTE: DNA extracted from salivary cells will be used for genotypic resistance studies when HIV-1 RNA levels in saliva are low (< 1000 HIV RNA copies/mL).

GENITAL SECRETIONS COLLECTION, PROCESSING,

STORAGE, AND SHIPMENTPROCEDURES

Subjects have the option to contribute either genital secretions or lymph tissues, or both, at study entry, weeks 16, 48, and 96, within 30 days of confirmedvirologic failure, and at the premature study discontinuation visit.

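### Appendix III freezes the labelled saliva tube before the section that fractionates liquid saliva, so the order of freezing and cell separation is unresolved and may differ between sites

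*Protocol*

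**What the plan says.** Appendix III has five sections: materials, collection, processing, storage and shipment, and analysis.

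- **Section 2.0 (collection).** The subject expectorates 5 mL into a tube held on wet ice. The site is told "Label the tube with PID, SID, and date". The next sentence reads "The sample should be frozen at -20ºC within 2 hours of collection and stored on site"; it goes on to give -80°C for that storage and dry ice for shipment, and ends with a pointer to section 4.0.
- **Section 3.0 (processing).** After the volume is measured, the instruction is "Vortex the specimen briefly and then transfer two 1-mL aliquots of whole saliva to sterile labeled cryostorage tubes". Then "Salivary cells are recovered from the remaining saliva sample as follows": the tube is spun at 400 x g "to pellet the cells, cellular debris, and mucins", and the supernatant is kept as cell-free saliva. The pellet is washed twice in PBS and resuspended. The site must then "count the cells using the hemocytometer and record" before aliquoting the cells.
- **Section 4.0 (storage).** Samples are kept at -80°C on site and then sent to the repository. No -20°C step is mentioned.
- **Section 5.0 (analysis).** RNA is quantified in saliva, with no fraction named. Proviral DNA is measured in salivary cells. In addition, "DNA extracted from salivary cells will be used for genotypic resistance studies when HIV-1 RNA levels in saliva are low", low meaning below 1000 copies/mL.

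**The concern.** A site that reads the sections in order freezes the tube it has just labelled. It then reaches instructions that cannot be carried out on a frozen tube, and has to improvise a thaw. Another site may see the difficulty, fractionate fresh saliva and freeze the aliquots. The two routes separate cells from fluid at different points: before any freezing in one, after a freeze and thaw in the other.

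Saliva is the only nonblood specimen required of every subject (Schedule of Events, footnote 8), and it enters all three primary objectives. Section 1.1 says that methods for nonblood samples lack standardization and offers this study as a uniform way of obtaining them. Two permissible orders for one specimen work against that aim. The introduction to section 4.0 of the protocol body says that compartment samples are stored and tested in batches later. A difference in handling might therefore be noticed only after the visits have passed, and a specimen frozen whole cannot be returned to its fresh state.

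**Working it through.** The plan states no figure to reproduce. The check sets the instructions side by side.

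1. **What is frozen.** The freezing sentence in section 2.0 directly follows the instruction to label the collection tube, and its subject is the singular *sample*. In section 3.0 *sample* means the unfractionated saliva: its volume is measured, the cells come from what remains of it, and the tube holding it is recapped. The products are called aliquots, cell-free saliva or cell suspension. Read consistently, section 2.0 freezes the raw specimen.

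2. **What processing needs.** Vortexing, pipetting, centrifuging, washing and counting all need liquid saliva. Section 3.0 has no thaw step. As ordered, the two sections do not join.

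3. **Time and place.** The only clock in Appendix III is the 2 hours to freezing. There is no separate limit on time to fractionation, and no statement that processing is done at the site.

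4. **Temperature.** The -20°C step appears only in section 2.0. Section 4.0 gives only -80°C. The text does not say when the specimen moves from one to the other.

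5. **Other specimens.** Appendix II has plasma processed and then stored at -70°C, within 48 hours. Appendix IV has semen processed within 4 hours and only the fractions frozen. Appendix IV has cervicovaginal lavage sent to the laboratory within set times, then spun, with the fractions frozen. For each of these the order is clear. For saliva it is not.

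6. **Which outputs depend on the order.**
   - Cell-free saliva is defined by the separation, so it is exposed.
   - The hemocytometer count is exposed.
   - Proviral DNA in salivary cells is exposed, and with it genotyping from that DNA when saliva RNA is low (secondary objective 2.22).
   - The whole-saliva aliquots are taken before separation and are not defined by it, so RNA measured in them is less exposed. Because section 5.0 names no fraction, RNA could come from either kind of aliquot.

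7. **Extent.** Of 5 mL collected, 2 × 1 mL is set aside whole, leaving 5 − 2 = 3 mL (3/5 = 60%) for separation. With 164 subjects and four scheduled collections (entry and weeks 16, 48 and 96), the instruction governs at most 164 × 4 = 656 scheduled specimens, plus those at failure and discontinuation visits. The share that would be frozen before fractionation is unknown. Any value from 0% to 100% (0 to 656 specimens) is compatible with the protocol.

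**The case against.** The strongest reply is that the intended order can be inferred. The freezing sentence points forward to section 4.0, which comes after processing. The materials list puts a centrifuge and cryostorage tubes beside the collection tube and wet ice. Section 3.0 makes no sense on a frozen tube, and the semen procedure fractionates first. On that reading, saliva is collected on ice, fractionated, frozen within 2 hours, stored at -80°C and shipped, and the 2 hours also bounds fractionation. This is probably what was meant, so the point is an unreconciled sequence and not a settled wrong instruction. It does not remove the point, because the text never says so, and its own use of *sample* points the other way.

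A reader might infer more: that freezing first ruptures the cells, that their DNA is thrown away in the washes, and that cell-free RNA, cell counts and cell DNA cannot be validly obtained. The documents do not support this. They give no figure for the effect of a freeze and thaw, and nowhere require that cells be intact or never frozen. The separated cells are themselves stored at -80°C in PBS, with no cryoprotectant mentioned, before the DNA assay. Material released before the first spin would largely be in the first supernatant, which section 3.0 keeps; only the later washes are discarded. Two whole-saliva aliquots are also retained and can supply RNA.

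**Conclusion.** The point stands as a conflict of sequence among sections 2.0, 3.0 and 4.0 of Appendix III. Followed in order, they freeze unfractionated saliva before cell separation, and sites may resolve the conflict differently. The cell-free fraction, the cell count and the salivary-cell proviral DNA, including its use for genotyping, may then not be comparable across sites. Whole-saliva RNA is less exposed. The planned week 48 saliva detection estimate (section 7.33, 50 subjects) is affected only to the extent that it rests on an exposed fraction.

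No size of bias can be given. That would need the share of specimens frozen first and the effect of freezing on each fraction, and the protocol has neither. The conclusion rests on the wording and order of the appendix, and on the assumption that at least some sites would follow the sections as printed. It is worth settling before collection starts, because the correction is cheap and the handling cannot be undone.

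**What to change.** In Appendix III:

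- Move the freezing sentence to after section 3.0 and apply it to the labelled whole, cell-free and cell aliquots.
- State that fractionation is done on site, on fresh saliva kept on wet ice, within a time limit confirmed by the laboratory. The existing 2 hours to freezing can serve.
- Reconcile the -20°C and -80°C steps between sections 2.0 and 4.0.
- State in section 5.0 which single fraction is used for saliva RNA. The choice between whole and cell-free saliva is the laboratory's; the text does not favour either.
- Record any specimen that was frozen before fractionation, so that it can be identified at analysis.

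The cost is a short rewording and one item on the processing record. Sites need bench time soon after collection, which the intended order would already require. Sample size and visit schedule do not change.
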